### Premature withdrawal

All subjects are free to withdraw from the study at any time. Investigators may also decide, for reasons of clinical safety, to withdraw subjects from the study. The date and justification for discontinuing the study is recorded in the patient’s medical record, in the patient’s data collection form and in the corresponding database.

### Data collection and measuring tools

Data are being collected from November 2022 to June 2023, in educational centres, primary care centres and diagnostic imaging centres. Organisation of data collection follows the procedure outlined in Table 1.

**Table 1 pone.0286586.t001:** Organisation of data collection procedures.

	Visit 1	Visit 2	Visit 3	Visit 4	Visit 5
	At educational centres	At primary care centres	At educational centres	At Diagnostic Imaging Centres	At the HUGTIP Hospital
Selection criteria					
Informed Consent					
Socio-demographic data					
Anamnesis and clinical history					
Physical examination					
Analytical determination					
Lifestyle assessment					
VCTE					
MRI					
Diagnostic tests / follow-up according to usual clinical procedure					

VCTE, Vibration-Controlled Transient Elastography; MRI, Magnetic resonance imaging.

**Socio-demographic data** include: age, sex, household income, parents’ education level, educational centre.

**Anamnesis and clinical history** include:

Comorbidities and pathological history: AHT, DM, dyslipidaemia, obesity or any other chronic diseases.Alcohol consumption: in standard drinking units (SDU).Tobacco consumption.Regular use of medication and/or other toxics.Family clinical history: family history of obesity, NAFLD, AHT, DM, dyslipidaemia and CVD.

**Lifestyle assessment** is self-reported online at the participating schools with the assistance of trained personnel.

Diet Quality estimation: KIDMED index [31] is used. It is based on 16 items with a dichotomous (yes/no) response format, and estimates adherence to the Mediterranean diet in children/adolescents. The index ranges from -4 to 12, and is based on a 16-question test. Answers are assigned a value of -1 or +1, respectively. The sums of these values are classified into 3 levels: a) >8, optimal diet; b) 4–7, improvement needed; c) <3, very low diet quality.PA assessment: PAU-7S [32] is used. PAU-7S consists of 7 questions referring to the week before the test. It takes different types of PA into consideration (walking; team sports; individual activity), as well as the context where it was practiced (schoolyard; after school and on weekends; physical education classes). The last question refers to whether the child was ill during the previous week or was unable to perform PA for some reason. Questions 1–6 are answered according to 5 possible options that refer to time spent (no activity, 0 minutes; <30 minutes; 30–60 minutes; 60–90 minutes; and >90 minutes. The questionnaire gives the total amount of minutes dedicated to PA in the week before the test is taken.Other child/adolescent lifestyle variables:
Sedentary behaviour is assessed by the Screen-time Sedentary Behaviour Questionnaire [33], which asks about time spent in: 1) watching TV, 2) playing computer games, 3) playing video games, 4) using mobile phone, separately for weekdays/weekends.Sleep duration is recorded by 4 questions on hours of sleep from the Sleep Habits Survey for Adolescents that ask about bedtime and time of waking up on weekdays/weekends [34].Consumption of sugar containing carbonated/no-carbonated beverages is assessed by standardized questions.

**Physical examination** is carried out by healthcare workers (minimum of 2) with participants in their underwear and barefoot.

Anthropometric data: weight (kg), height (cm), Body Mass Index (BMI) [38–40], waist circumference (WC) [40] and thoracic circumference.Tanner’s pubertal stage: it classifies and divides pubertal changes into five successive stages, ranging from infant (grade I) to adult (grade V).Determination of blood pressure.**Analytical determination** is performed on all subjects, after 12 hours of fasting, at the Primary Care Centre. It includes:Blood count, glucose, glycosylated haemoglobin, basal insulin levels, total cholesterol, high-density lipoprotein (HDL), low-density lipoprotein (LDL), triglycerides (TG), aspartate transaminase (AST), alanine transaminase (ALT), gamma-glutamyl-transpeptidase (GGT), alkaline phosphatase (ALP), total bilirubin, sideremia, transferrin, transferrin saturation index, total protein, albumin, urea, creatinine, sodium, potassium, thyroid stimulating hormone (TSH) and tiroxine (T4).Determination of insulin resistance using the HOMA method: blood glucose (mmol/L) x insulin (mU/L)/22,5.

**Metabolic Syndrome (MetS)** is determined according to the IDF consensus criteria for children and adolescents [36]. These include a WC at the ≥90th percentile and the presence of 2 or more of the following variables: 1) TG ≥150 mg/dl, HDL <40 mg/dl. 2) Blood pressure ≥130/85 mmHg. 3) Blood glucose ≥100 mg/dl or previously diagnosed DM.

**Liver fibrosis** is estimated by two methods: LSM and liver fibrosis scores.

LSM is performed in all patients using VCTE with the Fibroscan® (FS) system (Echosens, France). LSM is performed with S, M or XL probe following the Automatic Probe Selection tool available on the FS. The FS used is the 430 MINI. FS measures the hepatic elasticity of a cylinder approximately 1 cm in diameter by 4 cm in length [41]. FS transmits, via a probe, a vibration that propagates through the liver. The speed of propagation of the vibration correlates with the stiffness (in kPa) of the liver tissue and allows estimation of the fibrosis degree. In order for VCTE to be valid, 10 correct determinations with an interquartile range (IQR) <30 and a success rate >60% must be obtained. Significant liver fibrosis by VCTE is being defined by a LSM ≥6.5 kPa [13–16].Fibrosis scores/serum biomarkers: Pediatric NAFLD Fibrosis Index (PNFI) and Pediatric NAFLD Fibrosis Score (PNFS) are being used to estimate fibrosis degree. Significant liver fibrosis is being defined when the values of the different scores are above the following cut-offs, according to literature: PNFI ≥9, PNFS ≥13 [22, 23, 42, 43].

**Liver steatosis** is estimated using three methods: CAP, liver steatosis score and MRI.

CAP using VCTE is used to measure liver steatosis with the FS using either S, M or XL probe at the time of LSM. Liver steatosis is diagnosed when the value of CAP ≥225 dB/m [13–16].Liver steatosis is measured by the steatosis score Fatty Liver Index (FLI) which is based on: WC, BMI, TG and GGT [19]. Significant liver steatosis is defined when FLI ≥60 according to literature [44].Liver steatosis measured by MRI. It is performed using the Magneton Essenza 1.5 Tesla Aera system (SIEMENS), with the integration of Tim technology and Dot Engines (Day Optimizing through put Engines) application packages. The result obtained is the steatosis score or steatosis degree corresponding to the percentage of hepatocytes containing fatty vacuoles with respect to the hepatic fat fraction. Thus, a differentiation is made among mild steatosis (5–29% of hepatocytes affected), moderate steatosis (30–59% affected) and severe steatosis (more than 60% of hepatocytes affected). MRI is performed on all participants with altered VCTE results (≥6.5 kPa and/or ≥225 CAP) and 10% of participants with normal VCTE results (<6.5 kPa or <225 CAP).

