## Introduction

The increase of childhood obesity and its associated metabolic factors has led to an alarming rise in the incidence of non-alcoholic fatty liver disease (NAFLD) in this population. NAFLD is the accumulation of free fatty acids and triglycerides (TG) in the hepatocytes of individuals without toxic alcohol consumption and in the absence of other liver diseases. This pathology encompasses a wide spectrum of lesions ranging from simple steatosis to fibrosis, cirrhosis and even hepatocellular carcinoma [1].

NAFLD is the most common cause of liver disease and hypertransaminasaemia in the paediatric population, with a prevalence ranging from 7–9% and reaching 38–41% in obese children [2, 3]. Obesity is the main risk factor for NAFLD. The pathophysiological mechanisms are not yet fully understood, although the pathogenesis of NAFLD is considered to be multifactorial [4, 5]. The importance of early detection and appropriate management lies in its risk of progression to fibrosis and/or hepatocellular carcinoma along with its associated extrahepatic complications such as cardiovascular disease (CVD), diabetes mellitus (DM), insulin resistance (IR) and other endocrine and metabolic disorders like hypothyroidism or dyslipidaemia [6]. The presence of fibrosis is the major prognostic factor in NAFLD. Among children and adolescents with NAFLD, 25% have NASH and 14% have advanced fibrosis, the latter being more prevalent in paediatric patients with severe obesity than in adults with the same condition [7].

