### Sample size calculation

The school population aged between 9 and 16 in Mataró stands at 11,503 individuals [45]. These are approximately equally distributed between the 4 groups: male/female between 9 to 12 and 13 to 16 years old.

We expect that 8% of this population will have NAFLD and 2% will have liver fibrosis. A sample size of 2,866 students will allow us to estimate a prevalence of NAFLD stratified by age (9–12, 13–16 years) and sex of 8%, with a precision of 2% in each stratum, and a prevalence of fibrosis of 2%, with a precision of 1% in each stratum. We anticipate that blood samples will be available in 50% of the sample and MRI in 70%. MRI will be offered to all LSM/CAP positive subjects (LSM ≥6.5 kPa / CAP ≥225 dB/m) and, randomly, to 10% of those with negative LSM/CAP (LSM <6.5 kPa / CAP <225 dB/m). This will add up to 1,433 blood tests and 424 MRIs.

With the proposed sample we can find a concordance of 80% with a precision of 4% using kappa indices, or an intraclass correlation coefficient of 0,8 with a precision of 2,5% (8% and 4% precision for kappa and ICC, respectively, using only 424 MRIs). This sample size has been calculated assuming a design effect of 20%, an alpha error of 5%, a power of 80% and bilateral contrasts.

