### Statistical analyses

Prevalences of NAFLD and fibrosis will be calculated using CAP ≥225dB/m and LSM ≥6.5kPa, respectively. They will be calculated by sex and age (9–12 and 13–16 years) and 95% confidence intervals will be provided.To determine the optimal CAP cut-off point that best fits the 4 MRI categories, the relationship between CAP and MRI will be explored graphically, CAP means for each MRI category will be compared by ANOVA, 2-to-2 ROC curves will be used, and a multi-class ROC curve will be used to obtain the overall area under the curve for the finally chosen points. In addition, dichotomous CAP classifications (normal/altered) will be compared with MRI levels using contingency tables and chi-square tests.To identify the variables related to NAFLD, multivariate models will be used using NAFLD as the dependent variable and possible risk and confounding factors as independent variables.Concordance between the diagnosis of NAFLD or fibrosis obtained by different methods (CAP vs FLI, LSM vs PNFI, LSM vs PNFS) will be assessed by kappa indices (when using the dichotomised version of these variables) and by the intraclass correlation coefficient (when using the continuous version of the variables). The best cut-off point in PNFI and PNFS will be chosen to detect fibrosis using LSM ≥6.5 kPa as the standard test in the diagnosis of fibrosis using ROC curves.The construction of the biomarker to detect the presence of steatosis in children and adolescents will be carried out using the coefficients of multivariate logistic regression models, where steatosis (CAP >225 dB/m) will be the dependent variable and the rest of the variables will be potential explanatory variables that may form part of the marker.

To take into account that participants come from selected schools, hierarchical models will be used when necessary. All tests will be bilateral, with a significance of 5%. We do not plan to use missing data imputation methods as we expect very few missings beyond those already considered. Stata17 statistical package will be used.

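### Invalid VCTE scans are not allowed for and imputation is ruled out; if failures concentrate in children with obesity, the NAFLD prevalence is biased down by about 0.3 to 1 point at an assumed 1–3% invalid

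*Protocol article*

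**What the plan says.** In the protocol article, Data collection and measuring tools, the part on liver fibrosis sets the condition for a usable examination: "In order for VCTE to be valid, 10 correct determinations with an interquartile range (IQR) <30 and a success rate >60% must be obtained". The probe is matched to the child: "LSM is performed with S, M or XL probe following the Automatic Probe Selection tool available on the FS". Steatosis is read at the same examination: "CAP using VCTE is used to measure liver steatosis with the FS using either S, M or XL probe at the time of LSM". No separate validity condition is given for CAP.

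Under Statistical analyses, both prevalences of main aim 1 come from this examination: "Prevalences of NAFLD and fibrosis will be calculated using CAP ≥225dB/m and LSM ≥6.5kPa, respectively". No denominator is specified. The same section says of missing data: "We do not plan to use missing data imputation methods as we expect very few missings beyond those already considered". The incomplete items already considered are in Sample size calculation: "We anticipate that blood samples will be available in 50% of the sample and MRI in 70" per cent. Failed elastography is not among them. The expected prevalences are also there: "We expect that 8% of this population will have NAFLD and 2% will have liver fibrosis".

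The Introduction puts NAFLD prevalence at 7–9% in children generally, "reaching 38–41% in obese children".

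**The concern.** A validity rule on the measurement that defines the outcome creates missing outcomes. The case for not imputing rests on their number alone. For a prevalence, it also matters who is missing: a small loss does harm if the lost children have a very different prevalence. By the article's own figures, children with obesity have roughly five times the general prevalence of NAFLD, and large body size is a plausible reason for a failed or variable reading.

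If failures follow that pattern, the valid-scan prevalence is too low. The shift goes in one direction, does not shrink with more children, and is not reflected in the confidence interval. The flow in Study design sorts children only into altered or normal results, so there is no category for a child with neither.

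**Working it through.** **1. The plan's sample size.** Inputs from Sample size calculation: fibrosis 2% ± 1 point and NAFLD 8% ± 2 points in each of 4 strata, population 11,503 (about 2,876 per stratum), design effect 1.2, alpha 5% two-sided.

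- Fibrosis: n0 = 1.96² × 0.02 × 0.98 / 0.01² = 752.9. With finite population correction, 752.9 / (1 + 751.9/2,876) = 596.9. Times 1.2 = 716.2; times 4 = 2,865, against 2,866 stated. The figure reproduces.
- NAFLD: the same steps give 2,724, so the fibrosis target sets the size.

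Nothing in 2,866 is reserved for invalid scans.

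**2. Half-widths at 2,866.** 1.96 × √[p(1−p) × 1.2/n × (1 − n/N)] gives, for NAFLD, 1.89 points per stratum and 0.94 overall, and for fibrosis 0.97 per stratum. The overall figure is computed here; the article states precision per stratum only. With 5% or 10% of scans invalid, fibrosis becomes 1.01 or 1.04 per stratum.

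**3. Upper case: every failure is a child with obesity.** The article gives no failure rate, so f is assumed. The true prevalence is 8%, and q is the prevalence among failures (38–41%, Introduction). Valid-scan prevalence = (0.08 − f·q)/(1 − f).

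| Invalid overall (f) | Bias, q = 38% | Bias, q = 41% |
|---|---|---|
| 1% | −0.30 | −0.33 |
| 2% | −0.61 | −0.67 |
| 3% | −0.93 | −1.02 |
| 5% | −1.58 | −1.74 |
| 10% | −3.33 | −3.67 |

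Failure rate needed for a bias of b: f = b/(q − 0.08 + b). For b = 2 points, 0.02/0.35 = 5.7% (q = 41%) to 0.02/0.32 = 6.3% (q = 38%), about 164 to 179 of 2,866 children.

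**4. How extreme that is.** With 8% overall and about 40% in obese children, at most 0.08/0.40 = 20% of the sample can be obese, even if no other child has NAFLD. So 6% invalid, all in obese children, needs at least 0.06/0.20 = 30% of them to fail and nobody else; 10% invalid needs at least half.

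**5. Milder case: failures in both groups.** The obesity share o and the failure rates are assumed. The prevalence r in other children is solved from 0.08 = o·q + (1 − o)·r. Valid-scan prevalence = [o·q·(1 − f_ob) + (1 − o)·r·(1 − f_non)] / [o·(1 − f_ob) + (1 − o)·(1 − f_non)], with f_non = 2%.

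| Failure in obese | Bias, o = 10% | Bias, o = 15% |
|---|---|---|
| 10% | −0.25 to −0.27 | −0.37 to −0.41 |
| 20% | −0.56 to −0.62 | −0.85 to −0.93 |
| 30% | −0.88 to −0.97 | −1.34 to −1.48 |

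Ranges run from q = 38% to q = 41%. Example with o = 15%, q = 41%, f_ob = 20%: r = (0.08 − 0.0615)/0.85 = 2.18%, and (0.0492 + 0.0181)/(0.120 + 0.833) = 7.07%, a bias of −0.93. Overall failure in the first two rows is 2.8–4.7%.

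If validity is unrelated to obesity and to NAFLD status, the bias is zero.

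**The case against.** The strongest reply is that the article never says that invalid scans are excluded. The rule says the determinations must be obtained, which can be read as a standard for acquiring the scan, with measurement continued until it is met. The rule also stands in the LSM text, and the NAFLD argument needs it to reach CAP. Both points stand: exclusion, and extension to CAP, are inferences. They are still the ordinary reading, because the rule's subject is VCTE as a whole, CAP is taken at the same examination, and no other route is described.

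Second, automatic choice among S, M and XL probes bears directly on failure caused by body size. This is a real mitigation and makes low failure rates more credible. It does not say how the remaining failures are analysed.

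Third, a condensed article may leave scan handling to a fuller document. That is fair for repeat measurements and reporting detail. The decision not to impute, and its reason, are stated in the article itself.

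Three stronger readings are tempting and are not supported. A reader might infer that the bias will match or exceed the stated precision; that needs about 6% invalid, all in obese children, which sits badly with the expectation of very few missing values. A reader might infer that the fibrosis prevalence is biased too; the article gives no general-population fibrosis rate by obesity, so no such bias can be computed. A reader might call the sample too small for fibrosis; 1.01 to 1.04 points rounds to the stated 1%.

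**Conclusion.** The point holds in a limited form. The article defines validity for the measurement behind main aim 1, makes no allowance for invalid scans, and rules out imputation on an unquantified expectation. If invalid scans are dropped and concentrate in children with obesity, the NAFLD prevalence is biased down: about 0.3 to 1.0 points at 1–3% invalid when all are in obese children, and about 0.25 to 0.9 points with 10–20% failure in obese children and 2% in others. These are below the stated 2 points per stratum. The upper end is about the size of the computed overall half-width of 0.94.

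The sizes rest on assumed failure rates and obesity shares, and on the Introduction's 38–41% applying to CAP-defined NAFLD in the obese children whose scans fail. This is an inexpensive improvement to a main analysis and does not show that the design fails.

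**What to change.** Replace the blanket no-imputation sentence under Statistical analyses with wording along these lines:

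- State whether the validity rule applies to CAP as well as LSM, and how a child with an invalid scan is counted.
- Report the number and percentage of invalid scans by BMI class, age group and sex.
- Estimate the CAP and LSM prevalences with each valid scan weighted by the inverse of its estimated probability of being valid, or by multiple imputation. Use BMI for age, waist, thoracic circumference, age, sex and school.
- Show the valid-scan-only prevalence alongside.

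The body measurements belong to the Visit 1 physical examination, which is planned for all subjects, so no new data are needed. The cost is a wording change and a little more analysis. The correction assumes that validity depends only on these measured variables; if it also depends on liver fat among children of the same size, some bias remains. If very few scans are invalid, the two estimates will nearly agree, and the table by BMI class will show why.

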Diagnosis of NAFLD should be considered in paediatric population with excess weight, especially in those >10 years of age, with arterial hypertension (AHT), DM, IR or metabolic syndrome (MetS). In clinical practice, screening begins with anamnesis, physical examination, blood test and abdominal ultrasound, which help to establish a differential diagnosis with other entities. However, liver biopsy remains the gold standard for assessing disease progression, although its use is limited by its invasiveness and potential complications [8]. Some authors consider screening with transaminases, but these may still be normal in patients with NAFLD [5]. In terms of imaging, abdominal ultrasound, which is an affordable and safe technique, is only able to detect fatty infiltration above 30% [9]. Magnetic resonance imaging (MRI) is more accurate in diagnosing NAFLD, showing high sensitivity and specificity [10]. Nevertheless, its high cost and limited availability make it an invalid method for population screening.

Therefore, non-invasive serological and elastographic diagnostic methods are being developed. The most widely used is Vibration-Controlled Transient Elastography (VCTE), which non-invasively determines the presence of fibrosis by measuring liver stiffness (LSM) with the FibroScanⓇ (FS) device [11]. Multiple studies have demonstrated its usefulness in adults [11, 12], so it may also be appropriate for children and adolescents [5, 11]. Normal LSM values may vary according to age, ranging from 3.4–5.1 kPa [13, 14, 16]. Above this threshold, values correlate with different stages of fibrosis on the METAVIR scale: 5–7 kPa is indicative of F1; 7–9 kPa, F1-F2; and >9 kPa, F3-F4 [15, 16]. FibroScan features the Controlled Attenuation Parameter (CAP), which allows quantification of hepatic fat >11%. CAP values correlate with the degree of steatosis and a cut-off point of ≥225 dB/m is used for its detection [17, 18]. Furthermore, serological markers are used for diagnostic approaches to NAFLD and fibrosis. In adults, the Fatty Liver Index (FLI) [19] (NAFLD) as well as the NAFLD Fibrosis Score and FIB-4 (fibrosis) are commonly used [20] but these do not provide accurate results in the paediatric population [8, 21]. Thus, specific markers have been developed for these patients, such as the Pediatric NAFLD Fibrosis Index (PNFI) [22] and the Pediatric NAFLD Fibrosis Score (PNFS) [23], with an AUROC of 0.85 and 0.74 respectively [22, 23].

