### Specific outcome measures

Comparison of liver steatosis diagnosis accuracy between CAP by VCTE and Fatty Liver Index (FLI) in the general population aged ≥9 to ≤16 years.Comparison of liver fibrosis diagnosis accuracy between LSM by VCTE and two fibrosis scores (Pediatric NAFLD Fibrosis Index and Pediatric NAFLD Fibrosis Score) in the general population aged ≥9 to ≤16 years.Detection and structuring of the variables that constitute a specific biomarker for the paediatric-juvenile population that is capable of accurately determining the presence of hepatic steatosis.Correlation of liver steatosis diagnosis using CAP by VCTE, FLI and MRI, with the presence of lifestyles and socio-economic factors associated with NAFLD in the general population aged ≥9 to ≤16 years.Percentage of subjects with BMI ≥30 in the general population aged ≥9 to ≤16 years.Percentage of subjects with MetS according to the International Diabetes Federation (IDF) consensus criteria for children and adolescents [36] in the general population aged ≥9 to ≤16 years.

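### FLI is held at a fixed cut-off of 60 in 9–16-year-olds although the protocol calls it inaccurate in children, so its kappa with CAP cannot separate cut-off error from true disagreement

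*Protocol article*

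**What the plan says.** All references are to the protocol article.

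- **Introduction.** FLI is introduced as a score for adults. Of FLI and the adult fibrosis scores together it says that "these do not provide accurate results in the paediatric population".
- **Data collection and measuring tools.** FLI is one of three steatosis methods in this study, "which is based on: WC, BMI, TG and GGT". The call is made at a single value: "Significant liver steatosis is defined when FLI ≥60 according to literature". No adjustment for age or sex is given. The comparator is also a single value: "Liver steatosis is diagnosed when the value of CAP ≥225 dB/m".
- **Specific outcome measures.** CAP and FLI are compared for diagnostic accuracy. FLI also supplies one of three steatosis diagnoses in a second outcome: "Correlation of liver steatosis diagnosis using CAP by VCTE, FLI and MRI, with the presence of lifestyles and socio-economic factors".
- **Statistical analyses.** CAP–FLI agreement is assessed by kappa on the dichotomised variables and by intraclass correlation (ICC) on the continuous ones. CAP cut-offs are derived against MRI. For the fibrosis scores, "The best cut-off point in PNFI and PNFS will be chosen to detect fibrosis", using ROC curves. FLI has no such step.

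**The concern.** The protocol doubts FLI in children, then uses it at a fixed value in children, and withholds from it the threshold check that it gives to the two scores made for children.

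A fixed value is doubtful here on the protocol's own terms. Waist and BMI rise with growth between 9 and 16, so one absolute threshold does not mean the same thing at both ends of the age range. The protocol recognises this for metabolic syndrome, where waist is judged against the 90th percentile.

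What is at stake is interpretation. A low kappa could mean that FLI ranks children badly, or only that 60 lies in the wrong place on an index that ranks them well. These lead to different conclusions about FLI, and the plan as written cannot tell them apart. The FLI arm of the lifestyle and socio-economic correlation inherits the same uncertainty.

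**Working it through.** **1. The sample in which FLI can be computed.** Under Sample size calculation, blood is expected in 50% of 2,866 children: 0.5 × 2,866 = 1,433, as stated. The total also reproduces. For fibrosis at 2% ± 1% per stratum, n₀ = 1.96² × 0.02 × 0.98 / 0.01² = 752.9. With N = 11,503/4 = 2,875.75 per stratum, n = 752.9 / (1 + 751.9/2,875.75) = 596.9. Then 596.9 × 1.2 × 4 = 2,865, against 2,866 stated. At the expected 8%, the blood sample holds 0.08 × 1,433 ≈ 115 CAP-positive children, if blood donors resemble the whole sample.

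**2. How kappa depends on FLI's performance at 60.** Let p = 0.08 (CAP prevalence), s = sensitivity and f = false-positive rate of FLI ≥60 against CAP.

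- FLI-positive share: q = ps + (1−p)f
- Observed agreement: pₒ = ps + (1−p)(1−f)
- Chance agreement: pₑ = pq + (1−p)(1−q)
- κ = (pₒ − pₑ)/(1 − pₑ)

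Example with s = 0.50, f = 0: q = 0.04, pₒ = 0.96, pₑ = 0.0032 + 0.8832 = 0.8864, κ = 0.0736/0.1136 = 0.65.

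The documents give neither s nor f, so both are assumptions:

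| Sensitivity | κ, spec. 100% | κ, spec. 98% | κ, spec. 95% | CAP-positives missed of 115 |
|---|---|---|---|---|
| 10% | 0.17 | 0.12 | 0.06 | 103 |
| 30% | 0.44 | 0.36 | 0.27 | 80 |
| 50% | 0.65 | 0.55 | 0.44 | 57 |
| 70% | 0.81 | 0.70 | 0.58 | 34 |
| 90% | 0.94 | 0.83 | 0.70 | 11 |

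Kappa runs from 0.06 to 0.94 across this range, and nothing in the protocol says which row applies.

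**3. How much of that is the cut-off alone.** Hold the index fixed and move only the threshold, in an equal-variance binormal model: d = √2 · z(AUC), c = z(1 − f), s = 1 − Φ(c − d). The AUC is an assumption. Too high is taken as specificity 99.5% (f = 0.005). The Youden point is f = 1 − Φ(d/2), s = 1 − f.

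| AUC | κ, cut-off too high | Best κ at any cut-off | Difference | κ at Youden point |
|---|---|---|---|---|
| 0.75 | 0.08 | 0.22 | 0.14 | 0.15 |
| 0.85 | 0.20 | 0.38 | 0.18 | 0.25 |
| 0.95 | 0.53 | 0.64 | 0.11 | 0.48 |

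So the threshold alone can cost about 0.1 to 0.2 of kappa. If 60 sat at specificity 99.9%, the starting values would be 0.03, 0.09 and 0.34, and the differences 0.19, 0.29 and 0.30. Kappa also falls when the cut-off is too low. At AUC 0.95 the Youden point gives a lower kappa than the too-high cut-off. A new cut-off therefore does not guarantee a higher kappa.

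**4. Whether the ICC helps.** It does not use the threshold, but CAP is in dB/m with a positive call at 225 and FLI is an index with a positive call at 60. At their own thresholds the two differ by 225 − 60 = 165 units. An absolute-agreement ICC counts that offset as disagreement. A consistency ICC removes the offset but not the difference in spread. Neither shows how well FLI ranks children by steatosis; an AUC does.

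**The case against.** Testing an index at its published threshold, in a population where its accuracy is doubted, is a legitimate external evaluation, and a low kappa would truthfully say that FLI as published does not agree with CAP in children. This stands, and it is why 60 should be kept and reported. It does not help the reader who wants to know whether the index or only its threshold failed.

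The protocol also plans a paediatric steatosis marker by logistic regression, to which the FLI components could contribute. That goes further than moving one cut-off, but it yields a different score and does not answer the stated CAP-versus-FLI question.

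The reach is narrow. No main outcome uses FLI. The multivariate risk-factor models take NAFLD as outcome, and the same section defines its prevalence by CAP, so the lifestyle point concerns only the FLI arm of one specific outcome. Even there, FLI contains waist and BMI at every threshold, so a new cut-off would not free its correlates from body size.

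That 60 is an adult value is an inference: the protocol cites literature for it without naming the population. Finally, an extra ROC could be left to an analysis plan. But the article itself sets out the ROC step for PNFI and PNFS and states the FLI threshold, so the uneven treatment is visible in what is written.

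**Conclusion.** The inconsistency stands: the Introduction's caution about FLI, the fixed threshold under measurement, and the ROC step confined to PNFI and PNFS do not fit together. FLI ≥60 may misclassify children to an unknown extent, and the CAP–FLI kappa would mix that with true disagreement. Under the binormal assumptions the cut-off alone accounts for about 0.1 to 0.2 of kappa, and up to 0.3 if 60 is very extreme for this age group.

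A reader might go further and infer that FLI ≥60 will miss most affected children. The documents do not support this, because they give neither its sensitivity nor the distribution of FLI at these ages. Under-detection is plausible but unmeasured.

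A reader might also infer that kappa is bound to fall far short of a planned 0.80 because of the cut-off. That does not follow either. The 0.80 is a general input to the precision calculation, not a target for CAP against FLI. The possible kappas depend wholly on assumed sensitivities (0.44 at 30% and 0.81 at 70%, with perfect specificity). In the modelled cases no cut-off reaches 0.80, so such a shortfall would not be due to the threshold alone.

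This is a worthwhile improvement to specific outcomes and leaves the main results untouched.

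**What to change.** In Statistical analyses, add an FLI ROC analysis parallel to that for PNFI and PNFS:

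1. Use CAP ≥225 dB/m as reference in the blood sample. Use MRI steatosis as a further reference only with weights for the sampling, since MRI is offered to all VCTE-positives but only 10% of negatives. With equal uptake, each negative carries ten times the weight of a positive.
2. Report AUC, sensitivity and specificity overall and for ages 9–12 and 13–16.
3. Report kappa at the published 60 and at the sample-derived cut-off. Name the selection criterion beforehand, because the Youden point and the kappa-maximising point can differ widely at 8% prevalence. Correct the second kappa by bootstrap or cross-validation, since choosing and testing a cut-off in the same children is optimistic.
4. Show the FLI arm of the lifestyle correlation at both cut-offs.

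The cost is one more analysis on data already being collected. The sample-derived cut-off would need external validation before use elsewhere. The MRI version would be imprecise: if blood (50%) and MRI availability are independent, about 0.5 × 424 = 212 children have both, or roughly 106 per age group if these are equal in size. CAP is therefore the practical reference for the age-specific results.
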